## Abstract

**Background:**

Men have a special role to play in promoting maternal and child health during pregnancy, childbirth, and postpartum period. The health of women also requires the participation and cooperation of men. The aim of this study is to compare the effect of virtual and face-to-face childbirth preparation training for spouses of the primiparous women on the pregnancy experience, fear of childbirth (FOC), and mother- and father-infant attachment.

**Methods:**

The primiparous women attending the prenatal clinics of Lolagar Hospital and Azadi and Tehransar health centers of Tehran along with their husbands will be studied. The inclusion criteria for the women's husbands are the first experience of becoming a father, being at least 18 years of age, and the ability to read and write. The exclusion criteria for women's husbands are the history of physical/mental illness; being a smoker; and consuming alcohol, drugs, or psychotropic substances. The participants will be selected by the convenience sampling method and will be divided into three groups of study A, study B, and control. Spouses in study groups A and B will receive childbirth training through virtual and face-to-face methods with similar content, respectively. The control group only receives ordinary prenatal care. At the 18–20 weeks of gestation, demographic information, pregnancy experience scale (PES), and version A of Wijma delivery expectancy/experience questionnaire (WDEQ-A) will be completed. At 37-38 weeks of gestation, the PES and WDEQ-A questionnaires will be completed again and maternal postnatal attachment scale (MPAS) and postnatal paternal-infant attachment questionnaire (PPAQ) will be completed by the parents 12 weeks after the delivery. *Discussion*. Improving the experience of pregnancy, especially reducing the FOC and creating a positive attitude towards it, is a vital strategy to promote vaginal childbirth and reduce the number of cesarean sections requested by women. Achieving this will reduce the cost of health care and improve the quality of life during pregnancy, after childbirth, and during the growth and development of infants. *Ethics and Dissemination*. This research has been funded by the Iran University of Medical Sciences, approved by the Thailand Registry of Clinical Trials, and will commence in May 2020. Results will be disseminated through peer-reviewed journals and shared with the academic and medical community to pregnancy and childbirth outcomes. This trial is registered with TCTR20200515011.

## 1. Introduction

Improving maternal health is one of the important goals of the Millennium Development Goals. Given that pregnancy is one of the most sensitive periods in any woman's life, and most deaths that occur during pregnancy or childbirth are preventable, providing health care during and after the pregnancy is one of the main strategies for promoting the health of mothers and infants and preventing their mortality [1]. Men's participation during pregnancy increases women's acceptance of prenatal care [2], which reduces the negative behaviors of women and improves the outcomes of pregnancy [3]. On the other hand, the lack of participation and support of spouses in prenatal care is associated with increased postpartum depression, lack of desire for breastfeeding, and anxiety and stress in women [4, 5]. Women who are dissatisfied with their husbands' support during pregnancy are at higher risk for having a negative experience of childbirth [6]. The support of the husband during pregnancy leads to an increased ability of women to tolerate pressures and difficulties of pregnancy and childbirth [7]. On the other hand, factors such as experiencing and counting fetal movements [8], listening to music, having massage [9], receiving support from the family, friends, and spouse, having mother-child skin contact, providing kangaroo care immediately after birth [10], and receiving pregnancy training have a positive effect on attachment [11].

Men need training and information to support their wives during pregnancy [12]. Today, it is recommended to provide educational programs for the family, especially the husband to increase maternal support during pregnancy [5]. This training increases men's knowledge, attitudes, and performance in maternal health care and also improves couples' relationships; meanwhile, in most countries, men's participation in prenatal care is not common [13]. In Iran, it is not common for the husbands to intervene in pregnancy-related issues, even though there is no legal or Sharia prohibition in this regard [14]. This training can help men to accept their role and adapt to it even though it is sometimes difficult for them. Assessing men's educational needs in prenatal care is necessary before conducting the training [15].

Many member states of the World Health Organization (WHO) have prioritized men's participation in prenatal care as well as women's empowerment in their reproductive health programs to reduce mortality and inequality and improve women's health, as these two have synergistic and positive effects on each other [16]. Despite significant evidence on the beneficial effects of male participation in prenatal care, it has not yet been effectively promoted globally [14].

The results of studies on men's participation in supporting their spouses show that the level of participation varies in different parts of the world. The results of a study by Aliabedian et al. in Babol showed that 69% of Iranian men participate in prenatal care [17]. Mortazavi et al. reported 25% of men participated in prenatal care in Sabzevar, Iran [14], which could indicate a difference in social and cultural factors in these two regions of Iran [5]. However, compared to developed countries, the participation of Iranian men in prenatal care is low [14]. In a qualitative study by Mortazavi and Mirzaii to assess the causes, barriers, and outcomes of men's participation in pregnancy and childbirth care programs, their lack of knowledge about pregnancy, their workload, and the feminine atmosphere of health care centers were among the obstacles to men's participation in prenatal care [18].

By using new educational systems such as e-learning, we can overcome educational problems such as lack of time and special place for education and the need for experienced and trained people for education. E-learning can solve some of the problems that exist in our country in the field of childbirth preparation courses through its interactive, self-guiding, and flexible nature [19]. It is also essential to use different educational methods for men's participation in prenatal care [18]. Men's training programs are more successful if they are supported by the mass media, NGOs, and public education and are tailored to men's needs [15]. Considering the obstacles mentioned for men's participation in prenatal care and also the ease of access to the Internet and social media in Iran, the present study aims to compare the effect of virtual and face-to-face childbirth preparation training for spouses of the primiparous women on the pregnancy experience, fear of childbirth (FOC), and mother- and father-infant attachment.

### 1.1. Outcomes

The primary outcome of the present study is the pregnancy experience. The secondary outcome of the present study is FOC. In addition, the third and fourth outcomes are the mother- and father-infant attachment.

### 1.2. Hypothesis

The primary hypothesis of the present study is pregnancy experience score in the two intervention groups will be more positive from the control group. The secondary hypothesis in this study is the lower level in the fear of childbirth score in the two intervention groups compared to the control group. The third and fourth hypotheses are higher level in the score of parental attachment in the two intervention groups compared to the control group.

## 2. Materials and Methods

### 2.1. Setting

Data were collected in the prenatal clinics of Lolagar Hospital (study group A), Azadi health center (study group B), and Tehransar health center (control group) in Tehran, Iran, where the childbirth preparation courses are being offered in accordance with the educational programs of the Ministry of Health with high quality and in regular basis. It should be noted that the courses are held in groups of 10–12 people in the above-mentioned centers.

### 2.2. Inclusion and Exclusion Criteria

All 18–35-year-old pregnant women, who will be referred to the prenatal clinics of Lolagar Hospital as well as Tehransar and Azadi health centers and are eligible to receive prenatal care during the 18 and 20 weeks of gestation, will be asked to participate in the study. Inclusion criteria for women are to have Iranian nationality, be in gestational age of 18–20 weeks, have the ability to read and write, have single and low-risk pregnancy, and participate in childbirth preparation classes. Also, exclusion criteria for women are the history of infertility and physical/mental disease, being a smoker, and consuming alcohol, drugs, or psychotropic substances. The inclusion criteria for the women's husbands are the first experience of becoming a father, at least 18 years of age, Iranian nationality, the ability to read and write, and possession of smartphones or computers with access to the Internet and Telegram application until the end of the study. The exclusion criteria for women's husbands are the history of physical/mental illness and being a smoker, consuming alcohol, drugs, or psychotropic substances.

After the sampling, exclusion criteria would include preterm delivery or any symptoms of high-risk pregnancy, hospitalization in the neonatal intensive care unit, being absent for more than two sessions of childbirth preparation classes, and reluctance to continue with the study. In addition, the men of the study group A who do not send any feedback through Telegram application and the men of the study group B who do not attend more than one preparation sessions will be excluded from the study.

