### 2.3. Research Design and Sampling

This is a quasiexperimental study with a control group (parallel design) that will be performed on 114 primiparous women. Sampling will be done in three health centers. To complete the sampling in group A, the researcher will refer to Lolagar Health Center. Due to the presence of more husbands of nulliparous women in childbirth preparation classes, Azadi health center was allocated to complete the sampling process in group B, and finally Tehransar health center will be to complete the control group. Participants will be equally and not randomly divided into two study groups of A and B and one control group (Figure 1). Spouses of the participants in study groups A and B will be trained virtually and face-to-face, respectively. Also, the spouses in the control group will receive no education regarding childbirth preparation during pregnancy.

Based on the study's objectives, a Telegram channel called: “Virtual childbirth preparation courses for fathers” will be created for uploading the educational content. The educational contents will be provided based on the standard regulations of Iran.

To increase the quality of training and prevent sending the whole content at once, the content of each session will be provided in sections that will be uploaded at a specific time. The educational contents will include five videocasts, four PDF files, and eight video files, which are shown in Table 1.

To ensure that the messages sent on the Telegram social media are read by the participants, before joining the group, they will be asked to share their last seen status with the researcher. Moreover, they will be required to become online at least once a day to watch the videos or read the messages. The last seen time of the participants will be controlled by the researcher, and those who are not online, do not see messages, or do not give feedback for seven days are initially contacted through message. In case of receiving no answer, the researcher will contact them through a phone call to ask for the reason. If needed, another cell phone number will be obtained to resend a message by Telegram social media to that number. Otherwise, the participant will be excluded from the study.

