## 4. Discussion

This quasiexperimental clinical trial with the control group aims to compare the effect of virtual and face-to-face childbirth preparation training for spouses of the primiparous women on the pregnancy experience, FOC, and mother- and father-infant attachment. This study will be conducted by the Reproductive Health Department of the School of Nursing and Midwifery of Iran University of Medical Sciences, at the prenatal clinics of Lolagar Hospital and Azadi and Tehransar health centers. The main results of this study will help to improve the experience of pregnancy, reduce the FOC in pregnant women, and enhance the mother- and father-infant attachment.

To our knowledge, there are no published studies on the effect of two different educational methods on primiparous husbands on pregnancy experience, fear of childbirth, and parental attachment to the infant. This proposed project examines an educational intervention whose content is based on a qualitative study that investigates the educational needs of men to participate in prenatal care [15]. E-learning can solve some of the problems that exist in our country in the field of childbirth preparation courses through its interactive, self-guiding, and flexible nature. It is hoped that in such educational intervention two different educational methods will produce more favorable health outcomes. The use of new educational methods such as mobile software shows more desire of participants to participate in training classes. As a result, the strengths of this study will be the key to potential success. If e-learning can have the same effect on the outcomes of this study as face-to-face training, this method can be a useful way to increase the participation in childbirth preparation classes for those men who cannot attend childbirth preparation classes in person. If successful, the intervention may be adopted in other populations with other outcome and randomized clinical trial study designs. By using new educational systems such as e-learning, we can overcome educational problems such as lack of time and special place for education, and the need for experienced and trained people for education. Also, a range of outcomes relating to men's involvement in childbirth preparation courses will be assessed.

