The proposed study has a number of potential limitations. First, there is only a limited time in which the participants can be recruited. Second, due to the low attendance of men in childbirth preparation classes in many health centers, it is not possible to perform random allocation of participants in the groups. As a result, due to the nature of educational interventions, blinding of the participants is not possible in this study.

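### Husbands' ability to attend in person is not measured in any group, while the choice of centre and the attendance exclusion enrich group B for available husbands

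*Protocol article*

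**What the plan says.** Section 2.2 gives one set of entry criteria for husbands in all three groups, including "possession of smartphones or computers with access to the Internet and Telegram application until the end of the study". None of these criteria concerns ability to attend in person.

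Attendance by husbands enters elsewhere:

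- **Choice of centre (2.3).** "Due to the presence of more husbands of nulliparous women in childbirth preparation classes, Azadi health center was allocated" to group B. Each group has its own centre and allocation is not random.
- **Exclusion after sampling (2.2).** "the men of the study group B who do not attend more than one preparation sessions will be excluded from the study". Group A has a parallel rule for "the men of the study group A who do not send any feedback through Telegram application". No rule on husband engagement is given for control.
- **Delivery (2.3).** Group B's second and fourth sessions are held at Azadi with husbands present. The first and third are given as a booklet.

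The article treats in-person attendance as a real barrier. The Introduction reports that "their lack of knowledge about pregnancy, their workload, and the feminine atmosphere of health care centers were among the obstacles" to men's participation. The Discussion aims virtual training at "those men who cannot attend childbirth preparation classes in person" and gives as a limitation that "due to the low attendance of men in childbirth preparation classes in many health centers, it is not possible to perform random allocation".

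**The concern.** The groups are made alike on the access that virtual training needs, but not on the availability that face-to-face training needs. A husband who can and does come to a clinic session probably differs from one who cannot, for example in workload and in support for his wife. The Introduction links husbands' support to better maternal outcomes. If such men are more common in group B, B may look better than A and control for reasons unrelated to the training.

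Two comparisons are exposed: virtual versus face-to-face, which is the stated aim, and B versus control, which is half of the primary hypothesis. The Discussion hopes to show that e-learning does as well as face-to-face training, and that could be wrongly refuted. A versus control is not affected by this mechanism.

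**Working it through.** **1. Where selection can act**

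| Stage | Group B | Group A | Control |
|---|---|---|---|
| Entry criteria (2.2) | Common set | Common set | Common set |
| Reason for centre (2.3) | More husbands attend classes | None given | None given |
| Consent after full information (2.9) | Couple may decline if he cannot come | Couple may decline the daily online requirement | No husband commitment |
| Exclusion after sampling (2.2) | Non-attendance | No Telegram feedback | No husband rule |

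The first row is equal. The second and third act before training and the fourth during it. Only group B is selected on in-person availability. The wording of the B exclusion can mean attending at most one session or missing more than one. Under either reading it removes men who attend neither of the two in-person sessions.

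**2. What is measured**

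The T1 questionnaire (2.6) has four items on spouse support and none on ability to attend. PES and WDEQ-A are measured at T1 and T2, so a baseline exists for both. MPAS and PPAQ are collected only at T3 (2.4), so attachment has none. Section 2.7 plans ANCOVA without naming covariates.

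**3. The plan's own figure**

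The article states no figure for this bias. Its governing sample size, for fear of childbirth, reproduces (two-sided 5%, 80% power):

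n = (25.1² + 18.9²) × 7.849 / 15² = 34.44, rounded up to 35 per group. Adding 10% gives 34.44 × 1.1 = 37.9, so 38 per group and 114 in total.

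**4. Illustrative size**

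Let p be the share of available husbands in B, q the share in A or control, and D the outcome difference in SD between couples with available and unavailable husbands. Then

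bias = (p − q) × D.

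Assumed inputs:

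- p = 1, the extreme case.
- q = 0.25 to 0.69. These are the two prenatal-care participation figures in the Introduction, used only as a proxy for availability.
- D = 0.3 to 0.5 SD. This has no source in the document.
- No baseline adjustment.

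Results:

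- Smallest: (1 − 0.69) × 0.3 = 0.093 SD.
- Largest: (1 − 0.25) × 0.5 = 0.375 SD.
- On PES, at the planned SD of 7.5: 0.7 to 2.8 points.
- On WDEQ-A, with root-mean-square SD √((25.1² + 18.9²)/2) = 22.2: 2.1 to 8.3 points, or 14% to 56% of the planned 15-point difference.

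An unadjusted two-group test with 38 per group has its statistic shifted by bias × √(38/2), that is 0.405 to 1.635. The chance of a significant result with no training effect rises from 5% to about 7% to 37%.

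If p were 0.9 instead of 1, the range would be (0.9 − 0.69) × 0.3 = 0.063 to (0.9 − 0.25) × 0.5 = 0.325 SD.

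**5. Cost of restricting the comparison to available husbands**

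At q = 0.25, A or control keeps 38 × 0.25 = 9.5 couples. Comparing 38 with 9.5 on WDEQ-A, with d = 15:

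- SD 25.1 in the larger group: standard error √(25.1²/38 + 18.9²/9.5) = 7.36, power about 53%.
- SD 18.9 in the larger group: standard error √(18.9²/38 + 25.1²/9.5) = 8.70, power about 41%.

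The same formula gives about 84% with 38 in each group.

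**The case against.** A reader might infer that group B enrols only available husbands, so that its comparisons are already biased before training starts. The documents do not support that. Entry criteria are identical across groups, and attendance becomes a criterion only later, under the rules introduced by "After the sampling, exclusion criteria would include preterm delivery or any symptoms of high-risk pregnancy". Choosing a centre where more husbands attend makes available men more frequent, not universal. That couples decline at consent is a reasonable inference but is not stated. This objection stands, and the point is therefore one of enrichment.

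Three further arguments carry weight:

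- **Telegram is not only group A's tool.** Section 2.4 also uses it for data collection, so requiring it of all husbands has a study-wide reason. That weakens the contrast with Telegram but does not explain why availability is left unmeasured.
- **Group A selects too.** Its men must share their last-seen status and be online daily, and are excluded if they stay unresponsive. B versus A is therefore not available men against an unselected mixture. The selection is on a different trait, however, and need not cancel.
- **Some adjustment is possible.** Baseline PES and WDEQ-A and the spouse-support items could absorb part of the difference if used. No covariates are named, the support items are at best a partial proxy, and attachment has no baseline.

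The article also admits that allocation is not random and gives low male attendance as the reason. It does not discuss the imbalance in availability that follows.

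**Conclusion.** The point holds as a risk of enrichment. Group B is likely to contain more available, probably more supportive husbands than A or control, through the choice of centre, possible refusals at consent and the attendance exclusion. Nothing collected at T1 records availability. B versus A and B versus control are threatened, attachment most.

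The direction probably favours B, but that rests on the Introduction's link between husband support and outcomes. The size is unknown. The range of 0.09 to 0.375 SD, and the 7% to 37% false-positive rate, depend on the assumed availability shares, an unsourced 0.3 to 0.5 SD difference, complete availability in B and no baseline adjustment. They show that the bias could matter, not that it is present at that size. The change is worth making because availability cannot be cleanly recovered later.

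**What to change.** Section 2.2: at screening in all three centres, before the training format is described, ask whether the husband could attend two in-person sessions in the planned gestational weeks. Record yes or no. This is a measurement, not an entry criterion.

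Section 2.7: for B versus A and B versus control, include this answer as an ANCOVA covariate, together with baseline PES or WDEQ-A where available and the T1 spouse-support items. Keep all enrolled couples in the analysis, including those whom the attendance and feedback rules would now remove, so that the exclusion does not bring the selection back.

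Use restriction to husbands answering yes only as a sensitivity analysis, since it may leave about 9 or 10 of 38 couples in A or control.

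Discussion: state that group and centre remain confounded. The covariate reduces one known imbalance but cannot separate the training from the centre.

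Cost: one extra screening question and a small loss of precision from the covariate.

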On the other hand, participants in the study group B will receive face-to-face training, and the content of the first and third sessions will be provided to the spouses in the form of an educational booklet. The contents of the second and fourth sessions will be based on the third and eighth sessions of childbirth preparation classes at the Azadi health center with the presence of spouses. The teaching will be performed in the form of a lecture by the midwife using teaching aids for 90 minutes. Educational content will be taught in accordance with men's educational needs to participate in childbirth preparation classes reviewed by Simbar et al. [15]. Table 1 presents the time, content, and objectives of the educational courses that are similar for both study groups. To increase the generalizability of the results, another group will be considered as the control group, the members of which will receive no educational courses about pregnancy and childbirth preparation whether through social media or face-to-face. It is important to note that all three groups will receive ordinary perinatal care. In addition, all participants will be followed up until 12 weeks after delivery.

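### Husbands who engage poorly with training are removed after enrolment in groups A and B, with no matching rule in control, so comparisons with control are selected on engagement on one side

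*Protocol article*

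**What the plan says.** Section 2.2 lists exclusions that act after sampling. Two depend on the husband's engagement and name a group:

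- Group A: "the men of the study group A who do not send any feedback through Telegram application".
- Group B: "the men of the study group B who do not attend more than one preparation sessions will be excluded from the study".

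Section 2.3 adds a second rule for group A. A husband who is offline, does not see messages or gives no feedback for seven days is messaged, then telephoned, and another number may be obtained. "Otherwise, the participant will be excluded from the study".

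For control, section 2.3 says that "the spouses in the control group will receive no education regarding childbirth preparation during pregnancy".

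Other exclusions after enrolment name no group: "After the sampling, exclusion criteria would include preterm delivery or any symptoms of high-risk pregnancy, hospitalization in the neonatal intensive care unit", followed by "being absent for more than two sessions of childbirth preparation classes, and reluctance to continue with the study".

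Section 2.3 also states that "all participants will be followed up until 12 weeks after delivery". Section 1.2 sets the hypotheses as comparisons of the two intervention groups with control. Section 2.7 plans ANCOVA across the three groups and names neither covariates nor an analysis set.

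**The concern.** The engagement rules operate once training is under way, and they can only remove couples from A and B. Control keeps engaged and disengaged husbands alike. If couples with an engaged husband tend to have a better pregnancy experience, less fear or stronger attachment whatever the training, the retained intervention couples will look better than control even when training does nothing.

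The article's own background makes such a link plausible: the Introduction associates lack of spousal participation with anxiety and stress in women. The Discussion reports low attendance of men at classes in many centres, so removals could be more than occasional.

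The primary comparison is affected. Because the rule takes couples out of the study, and not merely out of one analysis, their 37-38-week and 12-week questionnaires may never be collected. A later analysis plan could not then recover them.

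**Working it through.** **Rules side by side**

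| Rule after enrolment | A | B | Control |
|---|---|---|---|
| Husband's engagement | No feedback (2.2); silent or offline and not reached (2.3) | Session attendance (2.2) | None possible |
| Preterm birth, high-risk symptoms, neonatal-unit stay | As written, yes | As written, yes | As written, yes |

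The first row is asymmetric against control, and it also differs between A and B. The second row is symmetric as written and does not select on engagement. It does condition on events after enrolment, which training might influence and which could differ by group.

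**Group B wording.** Section 2.3 gives the content of sessions 1 and 3 as a booklet, so only sessions 2 and 4 are live. Read literally, a husband must attend more than one session, hence both. Read in parallel with the neighbouring rule on absences, only a man who misses more than one, hence both, is removed. Under the literal reading, retention is settled only at session 4 in week 37 (Table 1), about when the 37-38-week questionnaires are due.

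**The plan's own sample size.** Inputs from section 2.5: SDs 25.1 and 18.9, difference 15, α = 0.05 (taken as two-sided), power 80%.

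n = (25.1² + 18.9²)(1.960 + 0.842)² / 15² = 34.4, so 35 per group, as stated. With 10% dropout, 34.4 × 1.1 = 37.9 or 34.4 / 0.9 = 38.3, consistent with 38; 3 × 38 = 114. The sample size is not in dispute.

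**Illustration of the bias.** Assume no true effect and a normal engagement score with correlation r to the outcome. The lowest fraction f is removed from one intervention group and none from control. Neither f nor r is in the document.

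- Bias in SD units = r × φ(z_f) / (1 − f).
- WDEQ-A SD = √[(25.1² + 18.9²)/2] = 22.2; PES SD = 7.5 (section 2.5).
- Type I error: two-sided z test, 38 control against 38(1 − f) intervention couples, allowing for the reduced variance after truncation.

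Results for r = 0.2 to 0.5:

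| f | φ(z_f)/(1 − f) | Bias, SD | WDEQ-A points | PES points | Type I error |
|---|---|---|---|---|---|
| 10% | 0.195 | 0.04-0.10 | 0.9-2.2 | 0.29-0.73 | 5.3-7.1% |
| 20% | 0.350 | 0.07-0.17 | 1.6-3.9 | 0.52-1.31 | 6.0-11.5% |
| 30% | 0.497 | 0.10-0.25 | 2.2-5.5 | 0.75-1.86 | 6.8-17.5% |

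Example: f = 30%, r = 0.5 gives 0.5 × 0.497 = 0.248 SD, and 0.248 × 22.2 = 5.5 points. None of these figures is adjusted for baseline.

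**Power.** For PES, Φ(7 / (7.5√(2/n)) − 1.96) is 0.95 at n = 30 and 0.93 at n = 27. For WDEQ-A, Φ(15 / √((25.1² + 18.9²)/n) − 1.96) is about 0.80 at n = 34, 0.74 at n = 30 and 0.70 at n = 27.

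**The case against.** Several points on the other side are sound.

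- **Pregnancy and neonatal exclusions.** A reader might group these with the engagement rules and say that both strip poorly engaged couples from A and B. They name no group and do not select on engagement, so they are a separate and lesser matter.
- **One missed lecture.** A reader might infer that a single absence removes a group B couple. That is only one of two readings.
- **Discarded data.** A neonatal-unit stay after a term birth is known only after the 37-38-week visit, so a reader might conclude that valid primary data will be thrown away. The article does not say that collected questionnaires are deleted, and an analysis plan not shown here may define the analysis set. The loss is conditional on the exclusion being carried into the analysis.
- **Follow-up sentence.** The statement that all participants are followed to 12 weeks can simply describe follow-up length for those still enrolled. It is unreconciled with the exclusions, not a clear contradiction.
- **Size.** The 10% dropout in section 2.5 is a natural starting point, and there the illustrated bias is modest. The contact steps in section 2.3 are meant to limit losses in group A.
- **Baseline adjustment.** PES and WDEQ-A are measured at baseline, and ANCOVA with those scores could absorb part of the selection. It need not absorb all of it, and the two attachment scales are measured only after birth, so they have no baseline.
- **Non-random centres.** Keeping every couple will not make the control comparison unbiased. That limitation is separate and partly acknowledged in the Discussion; the one-sided exclusion adds an avoidable component.

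None of this removes the asymmetry between trained and control husbands.

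**Conclusion.** The point holds for the husband-engagement rules. Applied as written, they select on engagement in A and B and not in control, and by different criteria in A and B. The likely direction against control is towards an apparent training benefit, if engaged couples do better; this is not proven.

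The magnitude is not computable from the document. The illustrated 0.04-0.10 SD at 10% excluded and 0.10-0.25 SD at 30% rests on assumed correlations of 0.2 to 0.5, a normal engagement score, no true effect and no baseline adjustment.

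Two stronger statements should be avoided. The bias should not be expressed as a share of the 15-point difference, because section 2.5 sets that difference between face-to-face and virtual training on a secondary outcome, not against control. Nor should the point be presented as a general loss of power: PES power stays at about 93-95% with 27-30 per group, and the 70-74% for WDEQ-A arises only under an assumed 20-30% loss from both groups.

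**What to change.** - In sections 2.2 and 2.3, replace exclusion from the study for poor feedback, lost contact or attendance with wording such as: *does not complete training but stays in follow-up unless consent is withdrawn*.
- Seek the 37-38-week and 12-week questionnaires from every enrolled couple. Include the wife's PES, WDEQ-A and MPAS when the husband cannot be reached; only the PPAQ depends on him.
- Analyse all available data in the group of enrolment. Keep PES and WDEQ-A data from couples with later preterm birth, high-risk symptoms or a neonatal-unit stay. For births before the 37-38-week assessment, this preserves the baseline and 12-week data.
- Use the feedback and attendance rules only to define a labelled secondary per-protocol analysis. Reconcile the two readings of the group B rule and the two group A rules, and align the follow-up sentence in section 2.3.

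The cost is mainly wording, plus some extra follow-up effort. Some PPAQ data will still be missing where fathers cannot be contacted, and the estimated effect may be smaller. The training is unchanged, and bias from allocating groups by centre remains.
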